It is recommended to administer 20–50 IE of Wilate® per kg/BW in vWF patients with acute bleeding. The dosage of Wilate® in this trial will be 2000 IU of vWF and 2000 IU factor VIII each in combination with one or two platelet concentrates. The medication (Wilate® or placebo and platelet concentrates) will be administered intravenously, because this is the only possible route of administration of Wilate® and platelets. The objective of this treatment is to stop the haemorrhage by administering the intervention drug once. Due to the long half-time of the study drug, a single administration will be sufficient for the 48-h observation period, also in cases where further thrombocyte transfusions are needed.

To make sure the study drug will be distributed within the body, a minimum waiting period of 10 min should be met whenever possible and depending on the clinical picture before platelet concentrate transfusion (usually this is the case as platelet concentrates have to be ordered in most situations). A waiting period of 20–30 min would be ideal. Thereafter, the clinical situation should be reassessed and the decision to transfuse a second platelet concentrate be taken after careful consideration.

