#### Laboratory parameters

Blood counts and global tests for coagulation, clinical chemistry biomarkers, vWF and FVIII levels and haemoglobin concentration will be analysed. Blood samples will be drawn during regular time points on the intensive care unit (e.g. 6 a.m.) except for the global platelet function analysis (VerifyNow®), which will be analysed right before the first study-specific platelet transfusion and 30–60 min after administration of the study drug and platelets.

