^g^Including von Willebrand factor ristocetin cofactor (VWF:Rco); factors II, V, and VII; INR; and platelets count and level of thrombin

^h^Beriplex, Cyklokapron, Konakion, Kyberin, Fibrogammin, NovoSeven, ionised calcium, etc. (see Additional file 1: Table S1)

**Table 3 Tab3:** ICU follow-up data to be assessed within the 48-hour study period beginning at study drug administration

	***Metavision®***	RedCap®
Administration of study medication (or placebo)		
Platelet function analysis (VerifyNow® ADP test) 30–60 min after administration of study drug		X
Check if informed consent is possible		X
Amount of blood loss since drug administration		X
Cause of bleeding (if occurred)		X
SOFA score	X	
Vital parameters^a^	X	
Lowest temperature measured^b^		X
Acidosis occurred (pH < 7.35)		X
Duration of acidosis		X
Full blood count^c^	X	
Coagulation laboratory^d^	X	
ROTEM	X	
Level of vWF and FVIII	X	
Haemoglobin concentration	X	
Fluid balance^e^	X	
Number of given RBCs	X	
Number of given FFPs	X	
Number of given platelet concentrates	X	
Amount of Prothromblex after study intervention	X	
Amount of tranexam acid after study intervention	X	
Amount of fibrinogen after study intervention	X	
Name/amount of other given coagulation products^f^	X	
Number of revision surgery for haemorrhage control		X
Transfusion-related side effects (AE, SAE, see 3.7)^g^		X
Thromboembolic events		X
Any recurrent bleeding such as cerebral haemorrhage, DIC		X

^a^Blood pressure, pulse, SpO_2_, ScvO_2_, SvO_2_ and respiratory rate

^b^Lowest temperature measured since ICU admission

^c^Hemoglobin, leucocytes, erythrocites, haematocrit, mean corpuscular volume (MCV), mean corpuscular haemoglobin (MCH), mean corpuscular haemoglobin concentration (MCHC), red cell distribution width (RDW), thrombocytes, quick, international normalised ratio (INR), activated partial thromboplastin time (APTT), thrombin time 1 (TZ1), and fibrinogen^d^ including factors II, V and VII; INR; platelets count; and level of thrombin

^e^Since ICU admission until 48 h after the study drug administration

^f^Beriplex, Cyklokapron, Konakion, Kyberin, Fibrogammin, NovoSeven, ionised calcium, etc. (see above)

^g^48-h observation period

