### Other outcome measures

#### Platelet function analysis

Before the administration of the study drug and 30–60 min after administration of the study drug, platelet function analysis (VerifyNow® ADP test) will be performed to evaluate the possible improvement of platelet function by timely adding vWF to platelets.

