#### Secondary analyses

##### Thrombocytes activity

The *T*-test evaluates the difference in the outcome between the two study groups. The outcome is defined as the difference in the platelet reaction units (PRU) measured with the VerifyNow® ADP test before and after the transfusion of TC.

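### The post-treatment VerifyNow sample is timed from the study drug in some places and from drug plus platelets in another, so it may be drawn before the transfusion it should follow is complete

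*Protocol article*

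**What the plan says.** The protocol article gives the time of the second VerifyNow ADP test in several places.

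- **Drug clock.** Table 3 lists "Platelet function analysis (VerifyNow® ADP test) 30–60 min after administration of study drug". The Platelet function analysis section, under Other outcome measures, says the same for both samples: "Before the administration of the study drug and 30–60 min after administration of the study drug, platelet function analysis (VerifyNow® ADP test) will be performed". Table 1 agrees: study medication is in the time-0 column and the second platelet function test is in the 30–60 min column.
- **Drug-and-platelets clock.** Laboratory parameters, under Safety outcome measures, places the test "30–60 min after administration of the study drug and platelets".
- **Analysis.** Thrombocytes activity, under Secondary analyses, compares the arms by t-test on the PRU difference "measured with the VerifyNow® ADP test before and after the transfusion of TC".

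Drug and platelets are not given together. In the Experimental intervention section, "a minimum waiting period of 10 min should be met whenever possible", and "A waiting period of 20–30 min would be ideal". That section also allows a second concentrate after reassessment. Adherence to intervention protocols gives a different minimum gap, 5 min, and plans a vWF activity sample half an hour after the platelet concentrate has ended. No section states how long a platelet concentrate takes to infuse.

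**The concern.** Staff following Table 3 and staff following Laboratory parameters would draw the same sample at different times, and both would be compliant. Only the second schedule, read as counting from the end of the platelets, guarantees a sample that fits the analysed outcome. Under the drug clock, part of the platelet dose may still be running when the sample is taken, the more so the longer the wait before the platelets.

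The stated purpose of the test is to show whether vWF given with platelets improves platelet function. If the second value is taken during the transfusion in some patients and well after it in others, the PRU change mixes different exposures. That widens the spread within each arm and makes the comparison harder to interpret. The primary outcome, its analysis and the sample size do not depend on this measurement.

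**Working it through.** The plan has no figure of its own to reproduce here. The check is timeline arithmetic.

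**Inputs**
- Drug given at t = 0.
- Wait w from drug to start of platelets: 5 min (Adherence to intervention protocols), 10 min minimum and 20–30 min ideal (Experimental intervention).
- Infusion time d for one concentrate: not in the document. Assumed range 15–60 min.
- Drug clock (Tables 1 and 3, Platelet function analysis): sample at t = 30 to 60.
- Drug-and-platelets clock (Laboratory parameters), read as counting from the end of the platelets: sample at t = w + d + 30 to w + d + 60.
- Samples assumed evenly spread over the 30–60 min window.

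**Step 1: earliest drug-clock sample relative to the start of platelets.** This is 30 − w and needs no assumption about d.
- w = 5: 25 min after platelets start
- w = 10: 20 min
- w = 20: 10 min
- w = 30: 0 min

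At every stated wait the platelets have started, or are just starting, when the window opens.

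**Step 2: do the two windows overlap?** Overlap = max(0, 30 − (w + d)) min. For example, w = 5 and d = 20 give 30 − 25 = 5 min. The overlap disappears once w + d reaches 30, that is at d = 25 for w = 5, d = 20 for w = 10 and d = 10 for w = 20. At w = 30 there is none for any d above 0.

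**Step 3: share of the drug-clock window before one concentrate has ended.** Share = (w + d − 30)/30, limited to 0–1. Example: w = 20, d = 30 gives (50 − 30)/30 = 67%.

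| Wait w (min) | d = 15 | d = 20 | d = 30 | d = 45 | d = 60 |
|---|---|---|---|---|---|
| 5 | 0% | 0% | 17% | 67% | 100% |
| 10 | 0% | 0% | 33% | 83% | 100% |
| 20 | 17% | 33% | 67% | 100% | 100% |
| 30 | 50% | 67% | 100% | 100% | 100% |

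Within the ideal wait, the share reaches 0% only if w + d is 30 min or less, for instance w = 20 with d of 10 min or less. Under the drug-and-platelets clock, read as above, it is 0% by definition.

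**Step 4: compare with the analysed outcome.** Thrombocytes activity needs a value after the transfusion. The drug clock ensures this only when w + d is at most 30 min, and the plan does not require that.

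**The case against.** A reader might infer more than the documents support.

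- *That many samples will precede the platelets.* This is not established. Step 1 shows that platelets have at least begun by 30 min at every stated wait, and with a 5–10 min wait and an infusion of 20 min or less no sample is early. The 20–30 min wait is an ideal, subject to the clinical picture.
- *That the two schedules are incompatible.* They partly overlap when wait plus infusion is under 30 min.
- *That the arm difference is pulled towards zero, so a null PRU result could not be read.* The documents do not show this. They describe vWF as enhancing adhesion independently of platelet count, so the added vWF could act on the patient's own platelets before the transfusion ends. Under randomisation and blinding, timing variation should be similar in both arms: noise rather than a difference created by timing.
- *That this is the only mechanistic evidence.* It is the only such comparison with a named test, but vWF and FVIII levels, vWF activity at four times and ROTEM are also collected.

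It can also be argued that Table 3 is shorthand, since the analysis and the stated aim both point to a post-platelet sample. That is plausible but not certain: Table 1 and the outcome definition also use the drug clock. Nor is this a detail left to a fuller document, because the article states the time repeatedly and the statements conflict.

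Finally, the test is listed under Other outcome measures, although its analysis stands under Secondary analyses. That limits the weight of the point.

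**Conclusion.** The inconsistency is real. Tables 1 and 3 and the outcome definition count from the study drug, Laboratory parameters counts from drug and platelets, and the analysis is defined across the transfusion. A drug-anchored sample may be drawn before the platelet transfusion is complete.

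The size cannot be fixed from the document. For an assumed infusion of 15–60 min, the early share is 17–100% at the ideal 20–30 min wait and 0–100% at a 5–10 min wait. These figures rest on the assumed infusion time, one concentrate and evenly spread sampling. A second concentrate, if counted, would lengthen the interval.

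The consequence is timing noise and a less interpretable PRU change. Its effect on precision cannot be quantified, because no PRU variance is given. No direction of bias is established. The point deserves correction but does not threaten the primary analysis.

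**What to change.** Use one sampling anchor in Table 1, Table 3, Laboratory parameters, Platelet function analysis and Thrombocytes activity: the end of the first study platelet concentrate. State how the sample is handled when a second concentrate is given, since without that the end of the transfusion is itself ambiguous. Draw the PRU sample together with the vWF activity sample already planned 30 min after the platelets end, and record the actual draw time and the end of the infusion so that off-window samples can be identified.

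Separately, the minimum drug-to-platelet waits in Experimental intervention and in Adherence to intervention protocols differ (10 and 5 min), and the sponsor should reconcile them. No view is taken here on which is right.

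The cost is wording in five places, one sentence on the second concentrate and the time fields. The change concerns sampling only and, because the draws are merged, needs no additional blood draw.

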### Secondary outcome measures

#### Number of platelet transfusions

This is the number of platelets transfused within the first 48 h after study allocation in both groups (Tables 2 and 3).

#### Quantity of blood loss

To calculate total blood loss during the first 48 h after the study, drug administration amount into drains and during surgery will be assessed and added up assessing chest tube drainage systems, cardiotomy reservoirs, drainages, suction units and rags, which will be measured and documented however possible. We will also document whether any further blood loss occurred that could not be measured over drainage (e.g. ‘open blood loss’ into surgical drains; Table 1).

#### Other secondary outcomes

Secondary outcome variables like ICU mortality, ICU length of stay, hospital mortality, hospital length of stay, number of bleeding events and number of revision surgeries/re-interventions for haemorrhage control are part of the routine clinical assessment for all hospitalised patients and will be documented accordingly. Patients or their family members will be contacted to assess the rehospitalisation rate, as well as 30-day and 1-year mortality.

### Other outcome measures

#### Platelet function analysis

Before the administration of the study drug and 30–60 min after administration of the study drug, platelet function analysis (VerifyNow® ADP test) will be performed to evaluate the possible improvement of platelet function by timely adding vWF to platelets.

#### Amount and costs of administered coagulation factors

Assessing the amount of administered coagulation factors/blood coagulation vitamins (i.e. 4-factor prothrombin complex concentrate, calcium, tranexamic acid, fibrinogen, coagulation factor XIII concentrate, vitamin K, antithrombin III, recombinant coagulation factor VIIa) will be ensured through documenting the administrated medications during the ICU stay. In addition, the estimated costs for the blood transfusion products will be registered (Tables 2 and 3; Additional file 1: Table S1).

## Reoperations and/or secondary interventions

Any reoperations or secondary interventions (e.g. bronchoscopy or gastroscopy) will be documented.

## Thromboembolic complications

Any thromboembolic events (e.g. venous thromboembolism, pulmonary embolus, stroke, myocardial infaction) occurring during the study period will be recorded.

## Additional bleeding events

Any bleeding events without the need for reoperation and/or secondary intervention requiring any type of additional transfusion (including administration of coagulation factors) will also be registered.

## Specific assessments

### VerifyNow® ADP test

The VerifyNow® assay (Accriva Diagnostics, San Diego, CA) is a turbidometry-based optical detection system that assesses the antiplatelet effect of aspirin and P2Y12 receptor inhibitors in the whole blood, similar to the light transmission aggregometry (LTA) technique [8]. Agonist-stimulated platelets bind to fibrinogen-coated polystyrene beads leading to aggregation and changes in light transmission. The test is performed using citrated whole blood with the addition of different activators including lyophilised ADP and prostaglandin E1. The result is shown as platelet reaction units (PRU) calculated from changes in light transmission. While VerifyNow® has been extensively studied among cardiology patients, mainly in North America, and is well established for these patients, experiences in the perioperative and ICU setting are limited.

In Switzerland, the VerifyNow® is distributed by Axon Lab AG, Baden-Dättwil. No specific handling of blood samples is required for VerifyNow®. After blood sampling in specific blood tubes, they will be placed into the device and the result of the test is provided on the screen.

### vWF:Rco test

Laboratory testing of the VWF ristocetin cofactor (vWF:RCo) will identify vWF activity by quantitative assessment of VWF protein adhesion to platelets or other particles and subsequent detection of the adhered VWF which is facilitated by the inclusion of ristocetin [9].

### Assessment of study drug side effects

Study drug side effects will be assessed as outlined in the ‘Safety outcome measures’ section.

### Assessments documented electronically

Either in our electronic case report form or due to direct data export from our patient data management systems (PDMS: Metavision ®, ISMed ®), we will document information listed in the tables and mentioned follow-up data.

## Randomisation

The trial staff will have permanent access to the electronic case report form where patients are screened and randomised to one of the study arms. Randomisation will be performed via the electronic case report form using REDCap® after checking the eligibility of the patient. A unique patient identification code will be assigned to every screened patient without possible inference to patient identity.

To achieve a balance in the participants in the two trial groups for a small sample size, we plan to perform the so-called block randomisation. The same principle will be performed for the randomisation of the study pack’s serial number. There will be no special criteria for discontinuing or modifying allocated interventions.

## Adherence to intervention protocols

Each time a platelet concentrate is prescribed, a red flag will appear in our data monitoring system. The vWF kit from Basel (HemosIL^2^) will be used to measure the vWF activity (vWF:Ac). The vWF:Ac is measured at four individual times per patient: baseline, 30 min after the thrombocyte concentrate administration has ended, the following day at 6 AM and the day after at 6 AM.

Because the study medication is only a few millilitres and should be given at least 5 min before giving platelets, handling it only for a few minutes will be enough to get it to room temperature, so the study medication will be kept in the fridge until randomisation.

## Blinding

The patient and the treating medical team will be blinded for the treatment. Wilate® and placebo are both provided with a syringe for drawing up the solution. Furthermore, the carton of Wilate® contains 2 Mix2Vial adapter (one for each vial), which is required for the preparation of Wilate®. Wilate® 1000 IU or placebo (sodium chloride 0.9% Fresenius) will be packed in identical-looking opaque cartons. The preparation occurs by unblinded site personnel.

The randomisation list will be maintained with a study-independent chief consultant and will be kept in a secured place in the ICU. To provide all-time immediate emergency unblinding, the storage location will be communicated to the research team. In case emergency unblinding is needed, a member of the study team will ask a study-independent physician to consult the randomisation list.

After the inclusion of all planned participants, the blinded data will be transferred to the responsible statistician for analysis and processing. A blinded analysis is planned after the recruitment of all 120 patients to assess the pre-defined effect size. In case of SAE, the patient will be unblinded for the trial arm.

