### Study population

#### Inclusion criteria

Participants fulfilling all of the following inclusion criteria are eligible for the study:Age ≥ 18 yearsAdmission to the intensive care unit (ICU)Patients needing platelet transfusion with or without severe bleeding or prior treatment with single or dual antiplatelet agents (ASS, prasugrel, clopidogrel, ticagrelor)Consent by the patient or a family member (non-emergency cases) in addition to the statement of an independent ICU physician

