### Primary outcome measure

#### Number of transfusions

This is the number of blood products (fresh frozen plasma (FFP), RBCs, platelet concentrates) transfused within the first 48 h after study allocation in both groups (Tables 2 and 3).

**Table 2 Tab2:** Baseline data assessed upon study inclusion (data prior/upon admission to ICU) to be documented *before* administration of the study drug

	***Metavision®***	***RedCap®***
Informed consent or statement of an independent physician		X
Randomisation, assignment of the group		X
Demographics^a^	X	
Admission diagnosis		X
Past medical history		X
Relevant medication prior to bleeding (1 month)^b^		X
Type of admission (medical, surgical)		X
SAPS II	X	
SOFA score	X	
Type of surgery (if applicable)		X
Cause of bleeding		X
Reason for thrombocyte transfusion		X
Amount of blood loss prior to ICU admission	X	
Vital parameters^c^	X	
Lowest temperature measured^d^	X	
Lowest temperature measured		
Fluid balance^e^	X	
Full blood count and chemogram^f^	X	
Coagulation laboratory^g^	X	
Platelets function analysis (VerifyNow® ADP test) *before* administration of the study drug		X
Number of given RBCs	X	
Number of given FFPs	X	
Number of given platelet concentrates	X	
Amount of prothromblex	X	
Amount of tranexamic acid	X	
Amount of fibrinogen	X	
Name/amount of other given coagulation products^h^	X	
Transfusion-related side effects (AE, SAE)	X	
Thromboembolic events	X	

^a^Age, sex, BMI, height, social security number (identification log only)

^b^NOACs, antiplatelet agents and oral anticoagulation such as Marcumar® (phenprocoumon), Eliquis® (apixaban), Lixiana® (edoxaban), Xarelto® (rivaroxabam), Pradaxa® (dabigatran), Aspirin ® (ASS) and Plavix® (clopidogrel)

^c^Blood pressure, pulse, SpO_2_, ScvO_2_, SvO_2_ and respiratory rate

^d^Lowest temperature measured before ICU admission

^e^In surgical patients from anaesthesia induction until ICU admission; non-surgical patients: fluid balance (if available) upon ICU admission

^f^Hemoglobin, leucocytes, erythrocites, haematocrit, mean corpuscular volume (MCV), mean corpuscular haemoglobin (MCH), mean corpuscular haemoglobin concentration (MCHC), red cell distribution width (RDW), thrombocytes, quick, international normalised ratio (INR), activated partial thromboplastin time (APTT), thrombin time 1 (TZ1), fibrinogen and β-subunit of human chorionic gonadotropin (βHCG) in female study participants of reproductive age < 45 years

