## Patient information and informed consent

The patients do not always have the capacity to give their consent for the study in advance or at all. In this study, the included patients will mostly be emergency cases. For this reason, an independent auditing physician will declare the patient’s suitability for trial participation in the patient’s name as his representative. As such, the independent physician safeguards the participant’s interest and ensures proper medical care. The signed document of the independent physician is the prevailing condition for the inclusion of the patient in our study.

Depending on the general condition of the patient, the investigators will explain to each participant the nature of the study, its purpose, the procedures involved, the expected duration, the potential risks and benefits and any discomfort it may entail upon enrolment. Each participant will be informed that participation in the study is voluntary and that he/she may withdraw from the study at any time and that withdrawal of consent will not affect his/her subsequent medical assistance and treatment.

If anyhow possible, the participant must be informed that his/her medical records may be examined by authorised individuals other than their treating physician.

All study participants will be provided a participant information sheet describing the study and providing sufficient information for the participant to make an informed decision about their participation in the study.

There will also be a consent form for the participant’s next of kin. The patient and next of kin information sheets and the consent forms will be submitted to the CEC to be reviewed and approved. Formal consent of a participant’s next of kin will be sought in non-emergency cases when the participant will be unable to give consent at any time, and if the next of kin is present or reachable over the phone, using the approved consent form. Consent of next of kin in non-emergency cases may be sought even after the inclusion of the patient. In case of ex-post-study withdrawal by the next of kin, patient data will be destroyed and therefore not be used for publication upon the next of kin’s wish.

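### Emergency unblinding by consulting a randomisation list kept in the recruiting ICU does not fully protect later assignments; a code break for one patient at a time would

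*Protocol article*

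**What the plan says.** Four parts of the Protocol article bear on this.

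- **Custody (Blinding).** "The randomisation list will be maintained with a study-independent chief consultant and will be kept in a secured place in the ICU". The next sentence adds: "To provide all-time immediate emergency unblinding, the storage location will be communicated to the research team".
- **Code break (Blinding).** In an emergency, "a member of the study team will ask a study-independent physician to consult the randomisation list". No procedure is described that would open a single patient's code. The same section says that a patient with an SAE is unblinded, but gives no route for this.
- **Issue of assignments (Randomisation).** REDCap issues the assignment once eligibility has been checked. Block randomisation is planned, and the same principle is applied to the serial numbers of the study packs. No block size is given.
- **Gate to inclusion.** Under Inclusion criteria, consent is required "in addition to the statement of an independent ICU physician". Under Patient information and informed consent: "The signed document of the independent physician is the prevailing condition for the inclusion of the patient in our study".

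Study setting names the ICU of the one participating hospital as the main place of recruitment, so the list is stored where patients are enrolled.

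**The concern.** The issue is concealment of assignments that have not yet been used, not the blinding of patients already treated. A person who looks up one patient in a list can see neighbouring rows. If those rows are future assignments, and if that person has a say in who enters, inclusion can depend on the coming arm.

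The safeguard is that custodian and reader are independent of the study. Independence of the study is not the same as distance from inclusion, because this trial also relies on an independent ICU physician to approve each entry. The people who may read the list and the people who may sign patients in can therefore come from the same group of doctors, and no sentence keeps them apart.

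At stake is selection by expected transfusion need, which bears directly on the primary count. Entry is broad, since patients needing platelets qualify whether or not bleeding is severe, and most inclusions are expected to be emergencies. Blinding after enrolment does not undo such selection. The covariates in the primary analysis remove only the part that they measure.

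**Working it through.** No figure in the plan is in dispute, so the check is mainly a reading of the sections together.

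1. **Where is the list, and who knows?** It is in a secured place in the ICU, held by a study-independent chief consultant, and the research team knows the location (Blinding). The consultant's department is not stated. Knowing the location is not access.
2. **What is opened in an emergency?** The list itself, by a study-independent physician at the study team's request (Blinding).
3. **Does the list show unused assignments?** Not stated. A block sequence is normally generated in advance, so a list with unused rows is the natural reading, and nothing limits the list to patients already randomised.
4. **Would an unused row reveal the next patient's arm?** Yes, if the list runs in enrolment order. If it runs by pack number, the reader must also know which pack comes next. The article does not say which applies.
5. **Can a reader of the list influence inclusion?** An independent ICU physician's signature is required (Inclusion criteria; Patient information and informed consent). No text says that this physician must differ from the one who consulted the list or from its custodian.

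Steps 1, 2 and 5 are on the page. Steps 3 and 4 are conditions. When both are met, foreknowledge by someone who signs inclusions is not excluded.

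**Illustration only.** The documents contain nothing from which a bias can be estimated. The following shows how the primary test would react under assumed values.

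- Inputs from Determination of sample size: 80% power, 5% level (two-sided assumed, since sidedness is not stated), 50% reduction. If the plan's power holds, the standard error of the log rate ratio is SE = ln 2 / (1.960 + 0.842) = 0.2474.
- Assumed: a share f of inclusions is made knowing the arm. Among these, placebo patients have r times the residual transfusion need of Wilate patients.
- With no drug effect, the expected rate ratio is m = 1 / (1 − f + f·r).
- Two-sided type I error = Φ(−1.96 + |ln m|/SE) + Φ(−1.96 − |ln m|/SE).

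| f | r | m | \|ln m\|/SE | Type I error |
|---|---|---|---|---|
| 0 | any | 1.00 | 0 | 5.0% |
| 0.1 | 1.5 | 1/1.05 = 0.95 | 0.197 | 5.4% |
| 0.2 | 1.5 | 1/1.10 = 0.91 | 0.385 | 6.7% |
| 0.2 | 2 | 1/1.20 = 0.83 | 0.737 | 11.4% |

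The first row is fully compatible with the documents. The last needs one inclusion in five to be steered, with a twofold difference in need.

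**The case against.** The case on the other side is substantial.

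- **Safeguards.** Storage is secured, the custodian is independent, the study team must ask an independent physician rather than look for itself, and REDCap assigns only after eligibility is checked. All of this stands and lowers the risk. It does not address an independent physician who has read the list and later signs an inclusion.
- **Screening.** All patients needing platelets are screened (Study period overview), and each platelet prescription raises a flag (Adherence to intervention protocols). Silently passing over a patient is therefore harder, and delay fits poorly with emergencies. Withholding a signature remains possible.
- **Silence on roles and list format.** The overlap of roles is not stated, only not excluded, and the list's order and content are unknown. This stands, and it is why the point is conditional.
- **Condensed article.** Code-break details and delegation of roles are often left to the full protocol. That would answer a complaint about omission. Here the article states a procedure, consultation of the list, and that procedure is weaker than an easily available alternative.

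A reader might infer three stronger claims that the documents do not support.

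- That people deciding on inclusion do know future assignments: nothing shows that any of them has read the list.
- That the list is opened at every SAE: consultation is described for emergency unblinding only, so the number of openings cannot be counted.
- That trial staff can see past arms and predict the next one from the blocks. Randomisation says: "The trial staff will have permanent access to the electronic case report form where patients are screened and randomised to one of the study arms", and Table 2 has the REDCap item "Randomisation, assignment of the group". Neither says that the arm is displayed to those users, and no block size is given. This point does not rely on it.

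**Conclusion.** The concern holds in a limited form. The stated procedure leaves open a route by which someone whose signature admits patients could have seen later assignments. The route requires that the list includes unused assignments, that its order lets them be linked to the next patient, and that the same physician both consults or holds the list and signs inclusions. The first is likely but not stated, the second is unknown, and the third is not excluded.

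No foreknowledge and no bias is demonstrated. The size cannot be derived from the documents, and the illustrative type I errors follow entirely from the assumed f and r. This is an inexpensive improvement to allocation concealment, not evidence that the randomisation has failed.

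**What to change.** Three changes to the Blinding section:

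1. Replace consultation of the list with a code break that reveals one patient only and is available 24 h. This can be a restricted unblinding role in REDCap or one sealed opaque envelope per pack number.
2. Hold the complete list outside the ICU, for example at the hospital pharmacy, which already provides the placebo, or at the Department of Clinical Research.
3. State that anyone who has seen the list or performed a code break may not sign inclusions as the independent physician, or screen or enrol patients.

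If the full protocol already provides a single-patient code break, it is enough to bring the article's wording into line and add the third sentence.

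The cost is a wording change, a REDCap user right or a set of envelopes, and a new storage place. Immediate emergency unblinding is kept. The downside is that a few ICU physicians become ineligible to sign inclusions.
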